#### Moderate PD

For the moderate PD unit, the primary outcome is the duration of the “OFF” period. The curative effect will be defined as “remission” by a ≥ 75% reduction rate, “response” for between 50 and 75%, “partial response” for between 30 and 50%, and “invalid” for below 30%.

Secondary outcomes will be Hoehn Yahr stage, Webster Clinical Symptom Scale (WCSS), UPDRSI-II for disease evaluation, Freezing of Gait Questionnaire (FOGQ) and abnormal involuntary movement scale (AIMS) to estimate MS; Wearing-off-9 Questionnaire (WOQ-9), Unified Dyskinesia Rating Scale (UDysRS), and Parkinson disease dyskinesia scale (PDYS-26) to estimate motor complications; PDSS-2, ESS, RBDSQ, NMSS, HAMD, HAMA, and SCOPA-AUT for assessing NMSs; the PDQ-39 for evaluating QoL; and the elderly quiver of TCM syndrome classification dysfunction score for TCM syndrome evaluation. UA and Hcy for disease prognosis, levodopa equivalent dose (LED), and the percentage of patients who increased their levodopa dosage will be considered in the overall response.

### Advanced PD

We used the PDQ-39 as the primary outcome of advanced PD units to evaluate the QoL of advanced PD patients. The curative effect will be defined as “remission” by a ≥ 75% reduction rate, “response” for between 50 and 75%, “partial response” for between 30 and 50%, and “invalid” for below 30%. Secondary outcomes are Caregivers Burden Inventory (CBI), bed rest, infection, hospitalization, and survival to evaluate QoL obliquely; Hoehn Yahr stage and UPDRS for disease evaluation; NMSS, mini-mental state examination (MMSE), and MoCA for assessing cognitive function; elderly quiver of TCM syndrome classification dysfunction score for TCM syndrome classification; and UA and Hcy for disease prognosis.

### Safety outcomes

Safety outcomes will be assessed at baseline and at the last visit, including red blood cell count (RBC), white blood cell count (WBC), platelet count (PLT), glutamic oxaloacetic transaminase (GOT), glutamic pyruvic transaminase (GPT), serum creatinine (Scr) and electrocardiogram (EKG). Laboratory results will be judged as abnormal if 20% out of the normal range or with supportive signs or symptoms. The WBC and EKG results should be judged based on the patient's specific situation.

#### Sociodemographic factors

Sociodemographic and clinical data, including sex, age, occupation, marital status, educational background, disease duration, and onset age, will be collected by baseline assessment.

### Biological specimen collections

Blood samples will be collected and measured using standard laboratory procedures; all samples will be destroyed after the data are reported.

### Sample size

The minimum necessary sample size by normal approximation was determined by the following formula [29]:$$n_{1} = n_{2} = 2 \times \left[ {\frac{{\left( {u_{\alpha } + u_{\beta } } \right)\sigma }}{\delta }} \right]^{2} + \frac{1}{4}u_{\alpha }^{2}$$

On the basis of our previous study, the estimated difference in the time of first addition of levodopa between the two groups among mild PD patients was 3.6 months, standard deviation (S.D.) 6.6. The estimated difference in the duration of the “OFF” period between the two groups among moderate PD patients was 4.6 min, S.D. 8.3. The estimated difference in the PDQ-39 score between the two groups among advanced PD patients was 7.3 points, S.D. 8.5. Considering a 5% significance level and a determined 0.10 β value, Uα/2 = 1.96, Uβ = 1.28, we calculated 72 cases are required in each group in the mild PD unit, 84 in the moderate PD unit, and 36 in the advanced PD unit. Considering a 20% drop-out rate, a sample of 172 subjects in the mild PD unit, 168 in the moderate PD unit, and 72 in the advanced PD unit is required, with a total of 412 participants enrolled in the study.

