**Methods:**

This study is designed as a multicentre, randomized, double-blind, placebo-controlled clinical trial. Patients will be stratified into 3 subgroups according to Hoehn & Yahr stage; 172, 168, and 72 participants will be required to be in the mild PD, moderate PD, and advanced PD subgroups, respectively, and will be randomized into the treatment or control group at a 1:1 ratio. The mild PD subgroup will receive a 48-week intervention, and the other 2 groups will receive a 24-week intervention. All groups will have a follow-up visit 12 weeks after starting the intervention. The intervention group will receive the Ziyin Pingchan formula, Jiedu Pingchan formula, or Fuzheng Pingchan formula, and the control group will receive the corresponding placebo. The primary outcomes will be the first addition of levodopa for the mild PD subgroup, the duration of the “OFF” period for the moderate PD subgroup, and the Parkinson's Disease Questionnaire (PDQ-39) for the advanced PD subgroup. The secondary outcomes will also be verified by subgroups, including the Unified Parkinson’s Disease Rating Scale (UPDRS), Parkinson’s Disease Sleep Scale-2 (PDSS-2), scales for Outcomes in Parkinson’s Disease—Autonomic (SCOPA-AUT), and the nonmotor symptom scale (NMSS).

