### Statistical methods

Statistical analysis will be performed using SPSS 25.0 software. Measurement data will be presented as the mean ± S.D. Comparisons between two groups will be conducted using Student’s t-test or the Mann–Whitney U test. Quantitative data will be reported as percentages and proportions, and comparisons between two groups will be performed by χ2 or Fisher’s exact tests. The Mann–Whitney U test will be used to compare the ordinal data. Multivariate analysis will be performed using analysis of variance (ANOVA) or generalized estimation equations (GEE). All analyses will use two-tailed tests with a P value of 0.05 as the threshold for significance.

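### The per-group requirements of 84 (moderate) and 36 (advanced) are drop-out-inflated figures reported as pre-drop-out ones; the stated formula gives 72, 70 and 30

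*Protocol article*

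**What the plan says.** The Sample size section opens with "The minimum necessary sample size by normal approximation was determined by the following formula", which is the two-sample formula for means with an added term of one quarter of the squared alpha quantile. It gives a difference and standard deviation for each unit (for the first, "mild PD patients was 3.6 months, standard deviation (S.D.) 6.6"), then the error rates ("Considering a 5% significance level and a determined 0.10 β value") and the quantiles ("Uα/2 = 1.96, Uβ = 1.28").

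The results follow in two sentences. The first gives the number per group: "we calculated 72 cases are required in each group in the mild PD unit, 84 in the moderate PD unit, and 36 in"; the last figure is for the advanced unit. The second adds the allowance: "Considering a 20% drop-out rate, a sample of 172 subjects in the mild PD unit, 168 in the moderate PD unit"; it continues with a total of 72 for the advanced unit, which makes 412 in all. The Methods part of the abstract repeats the totals only: "172, 168, and 72 participants will be required". Under Statistical methods, two-group comparisons use Student's t-test or the Mann–Whitney U test, and "All analyses will use two-tailed tests with a P value of 0.05 as the threshold for significance".

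**The concern.** The order of the two sentences tells the reader that 72, 84 and 36 are the numbers before drop-out and that 172, 168 and 72 are the totals after it. That fits the mild unit, where 2 × 72 = 144 rises to 172. It does not fit the other two, where 2 × 84 = 168 and 2 × 36 = 72 are already the final totals. Either two of the three units have no allowance, or two of the three per-group figures are not what the text says they are.

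Each unit has its own primary outcome and is sized separately, so each per-group figure has to stand alone. A reader who takes 84 and 36 as evaluable requirements would conclude that any drop-out leaves those units underpowered. On that reading, dividing by 0.8 would call for 210 and 90 participants instead of 168 and 72.

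**Working it through.** **Inputs**, all from the Sample size section: quantiles 1.96 and 1.28; differences and SDs of 3.6 and 6.6 months (mild), 4.6 and 8.3 minutes (moderate), 7.3 and 8.5 points (advanced); drop-out 20%; totals 172, 168 and 72. Allocation is 1:1 (Randomization section).

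**Step 1. The printed formula.** n per group = 2 × [(1.96 + 1.28) × SD / difference]² + 1.96²/4, where 1.96²/4 = 0.9604.

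- Mild: 2 × (3.24 × 6.6/3.6)² + 0.9604 = 70.5672 + 0.9604 = 71.53, so 72. Stated 72: reproduced.
- Moderate: 2 × (3.24 × 8.3/4.6)² + 0.9604 = 68.3535 + 0.9604 = 69.31, so 70. Stated 84: not reproduced.
- Advanced: 2 × (3.24 × 8.5/7.3)² + 0.9604 = 28.4651 + 0.9604 = 29.43, so 30. Stated 36: not reproduced.

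**Step 2. Would another convention give 84 and 36?** Without the added term, the two-sided numbers are 71, 69 and 29. One-sided they are 58, 56 and 24. Neither variant does.

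**Step 3. Where the figures come from.** 70 × 1.2 = 84 and 30 × 1.2 = 36, both exact. For the mild unit, 72 × 1.2 = 86.4 per group, or 172.8 in total, against 172 stated. A single multiplier of 1.2 therefore explains all three totals, apart from rounding down in the mild unit. The first results sentence mixes one figure before inflation (72) with two after it (84 and 36).

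**Step 4. What the totals allow for.** Enrolled per group: 86, 84 and 36. The largest loss that still leaves the rounded requirement is:

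- Mild: 1 − 72/86 = 16.3%
- Moderate: 1 − 70/84 = 16.7%
- Advanced: 1 − 30/36 = 16.7%

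To keep the requirement after 20% loss, one divides by 0.8: 90, 87.5 and 37.5, so 90, 88 and 38 per group. The totals would be 180, 176 and 76, or 432 against 412.

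**Step 5. Power at 20% loss with the planned enrolment.** Remaining per group: 0.8 × 86 = 68.8, 0.8 × 84 = 67.2 and 0.8 × 36 = 28.8.

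| Unit | n per group | Printed formula, inverted | Two-sided t-test (noncentral t) | Plain normal approximation |
|---|---|---|---|---|
| Mild | 68.8 | 88.8% | 88.8% | 89.2% |
| Moderate | 67.2 | 89.1% | 89.1% | 89.5% |
| Advanced | 28.8 | 89.3% | 89.3% | 90.3% |

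The inverted formula is: power = Φ[(difference/SD) × √((n − 0.9604)/2) − 1.96]. With no loss at all, t-test power at 86, 84 and 36 per group is 94.5%, 94.6% and 94.9%.

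**The case against.** The strongest reply is that nothing in the design is harmed. If 84 and 36 are 70 and 30 with the allowance built in, the allowance exists and only its label is wrong. The enrolment totals follow one consistent rule. The article ties no interim re-estimation, evaluable-number rule or recruitment stop to 84 or 36, and the abstract repeats only the totals. Multiplying by 1.2 where one should divide by 0.8 is a common loose usage, and here it costs about one point of power. The differences and SDs are themselves estimates from a previous study, and modest error in them would outweigh that point.

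Most of this stands, and it sets the severity. It does not remove the error: the formula, inputs and results are all printed, two of the three results do not follow, and no other section corrects them.

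Two stronger readings are tempting, and the document supports neither. A reader might infer that the moderate and advanced units were planned with no margin for drop-out. The text does read that way, but 84 and 36 exceed the formula's requirement by exactly the factor 1.2. A reader might also infer that every unit is underpowered and that more recruitment is needed. The shortfall is 0.7 to 1.2 points under the t-test. In the advanced unit it depends on the method, since the plain normal approximation gives 90.3%.

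**Conclusion.** The stated requirements of 84 and 36 per group are wrong as written: the printed method gives 70 and 30. They are overstated by 20% as pre-drop-out figures and correct as enrolled figures under a multiplier of 1.2. That origin is an inference from the arithmetic, since the article does not show the inflation step, but it accounts for all three totals.

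The secondary point is small. The enrolment absorbs about 16 to 17% loss instead of the stated 20%, and at 20% loss power is about 89% in each unit against a stated 90%.

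These results take the printed formula, differences and SDs as given, equal groups, loss shared evenly between arms, and Student's t-test, which is one of the two tests named. Severity: a minor correction of stated figures, with no case here for changing enrolment.

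**What to change.** Keep enrolment at 412 and replace the two results sentences in the Sample size section with wording such as:

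> The formula gives 72, 70 and 30 evaluable participants per group in the mild, moderate and advanced units. Enrolling 86, 84 and 36 per group (172, 168 and 72; 412 in total) keeps 90% power with up to about 16% drop-out, and gives about 89% power at 20% drop-out.

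The totals in the abstract need no change. The cost is one reworded paragraph and a stated power at 20% loss about one point lower. If the sponsor prefers to claim 90% power at 20% loss, the totals would be 180, 176 and 76 (432), which is 20 more participants; the small gain does not require it.

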### Statistical methods

Statistical analysis will be performed using SPSS 25.0 software. Measurement data will be presented as the mean ± S.D. Comparisons between two groups will be conducted using Student’s t-test or the Mann–Whitney U test. Quantitative data will be reported as percentages and proportions, and comparisons between two groups will be performed by χ2 or Fisher’s exact tests. The Mann–Whitney U test will be used to compare the ordinal data. Multivariate analysis will be performed using analysis of variance (ANOVA) or generalized estimation equations (GEE). All analyses will use two-tailed tests with a P value of 0.05 as the threshold for significance.

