### Randomization

Stratified group randomization will be applied in this study. Allocation will be applied by block randomization stratified by study centre with block sizes of 4 using SPSS 25.0 software, and the subjects will be randomly divided into the intervention group or control group (Seed Number: 202106151) in a 1:1 ratio. The randomization sequence will be kept in sealed opaque envelopes and will be prepared and preserved by the pharmaceutical company. Researchers in charge of enrolment and evaluation will be blinded to the patient allocation. After the participants are enrolled, they will be given an enrolment number by the sequence they take part in the study, and then they will be given the investigational medicinal product (IMP). An emergency unblinding envelope will be set for each blind code, indicating to which group the subject is assigned and what medication intervention the participant is receiving. Those sealed opaque envelopes will be sent to each study centre together with the study medications of the corresponding blinding code. Each centre will assign a research assistant responsible for allocating the drugs to the participants, and emergency unblinding envelopes will be kept by them.

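### The named two-group tests for OFF duration and PDQ-39 are valid but use neither the baseline values nor the centre strata, so they forgo precision the trial could have at no cost

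*Protocol article*

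**What the plan says.** The Statistical methods section of the protocol article sorts tests by type of data. For measurement data: "Comparisons between two groups will be conducted using Student’s t-test or the Mann–Whitney U test". It gives no rule for choosing between the two and no covariate or stratum. It then adds: "Multivariate analysis will be performed using analysis of variance (ANOVA) or generalized estimation equations (GEE"), without saying which outcome this serves, which terms enter, or whether it is primary. On significance: "All analyses will use two-tailed tests with a P value of 0.05 as the threshold for significance".

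The Randomization section says: "Allocation will be applied by block randomization stratified by study centre with block sizes of 4". Study setting lists seven centres.

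OFF duration is the primary outcome of the moderate unit and PDQ-39 that of the advanced unit. Table 2 schedules both at enrolment and again at weeks 12 and 24 and at follow-up. The outcome sections also grade each by percentage reduction, which uses the baseline value but not as a covariate. They state no primary time point.

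The Sample size section sizes every unit with a formula for the unadjusted difference of two means: "Considering a 5% significance level and a determined 0.10 β value, Uα/2 = 1.96, Uβ = 1.28". The inputs that matter here are, for OFF duration, "between the two groups among moderate PD patients was 4.6 min, S.D. 8.3", and for PDQ-39, "The estimated difference in the PDQ-39 score between the two groups among advanced PD patients was 7.3 points, S.D. 8.5".

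**The concern.** Two pieces of information bought by the design enter no stated analysis.

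- **Baseline.** A score measured on the same scale before treatment usually predicts the later score. Put into the model, it removes the variance it explains from the comparison.
- **Centre.** Blocking within centre balances the arms on centre differences. An analysis that omits centre leaves those differences in the error term, so it reports a standard error somewhat larger than the true one.

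The open choice between two tests is a related weakness. The t-test compares means and the Mann–Whitney U test compares distributions by rank. With no stated rule, the hypothesis tested could come to depend on the data.

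At stake is mainly precision, most of all in the advanced unit with 36 enrolled per arm, and with it a single, fixed primary analysis.

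**Working it through.** **1. Reproduce the plan's figures.** With the article's formula, n per group = 2[(1.96 + 1.28) × SD/δ]² + 1.96²/4:

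| Unit | δ | SD | n per group | × 1.2, rounded up | Both arms | Stated total |
|---|---|---|---|---|---|---|
| Mild | 3.6 | 6.6 | 71.53 | 86 | 172 | 172 |
| Moderate | 4.6 | 8.3 | 69.31 | 84 | 168 | 168 |
| Advanced | 7.3 | 8.5 | 29.43 | 36 | 72 | 72 |

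The totals reproduce, so the trial was sized for an unadjusted comparison.

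**2. Unadjusted power after 20% loss.** Evaluable per arm: 84 × 0.8 = 67.2, taken as 67; 36 × 0.8 = 28.8, taken as 28. The standard error is SD × √(2/n), and power comes from the noncentral t distribution at two-sided 0.05.

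- Moderate: 8.3 × √(2/67) = 1.434; 4.6/1.434 = 3.21; power 89.0%.
- Advanced: 8.5 × √(2/28) = 2.272; 7.3/2.272 = 3.21; power 88.4%.

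A normal approximation gives 89.4% and 89.5%. Either way the planned 90% is nearly met.

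**3. Power with baseline and centre in the model.** The documents do not give the baseline–outcome correlation ρ, so 0.3, 0.5 and 0.7 are assumed. They also do not say whether the stated SD is of the final value or of the change, so both are shown. The residual SD is:

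- SD × √(1 − ρ²), if the stated SD is of final values;
- SD × √((1 + ρ)/2), if it is of change, with equal variance at both times.

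Seven degrees of freedom are taken for the extra terms (one for baseline, six for seven centres). No variance is credited to centre.

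| ρ (assumed) | Moderate, SD of final value | Moderate, SD of change | Advanced, SD of final value | Advanced, SD of change |
|---|---|---|---|---|
| 0.3 | 91.6% | 97.7% | 91.0% | 97.4% |
| 0.5 | 95.7% | 95.7% | 95.3% | 95.3% |
| 0.7 | 99.4% | 93.2% | 99.3% | 92.7% |

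At ρ = 0.5 the residual variance is 1 − 0.25 = 0.75 of the unadjusted variance, which is equivalent to 1/0.75 = 1.33 times as many patients. Without the extra terms the advanced unit has 95.4% at ρ = 0.5, so the lost degrees of freedom cost about 0.1 point.

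**4. Effect of omitting centre.** If a share ICC of the variance lies between centres and the arms are balanced within centre, the reported standard error exceeds the true one by the factor 1/√(1 − ICC). The true two-sided error rate is then 2[1 − Φ(1.96/√(1 − ICC))].

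| ICC (assumed) | Standard error too large by | True error rate |
|---|---|---|
| 0.01 | 0.5% | 0.049 |
| 0.05 | 2.6% | 0.044 |
| 0.10 | 5.4% | 0.039 |

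A simulation with seven centres, blocks of 4 and ICC 0.05 (2,000 runs per setting) gave type I error of 4.5% to 5.7% for the t-test, and a mean standard error within about 3% of the empirical one. The effect is small and, by the formula, conservative.

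**The case against.** **The article ties no test to a primary outcome.** A reader might infer that it fixes unadjusted tests as the primary analyses. It does not say so. The tests are listed by data type, ANOVA and GEE could carry baseline or centre, and an analysis plan not shown may settle the model. This stands as a limit on the claim. Still, the t-test and the Mann–Whitney U test are the only two-group methods named for such data, the sample size rests on the same comparison, and the ANOVA/GEE sentence supplies no adjustment as written.

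**The tests are valid.** A reader might also infer that the standard errors are wrong in a way that threatens the conclusions. They are not. Omitting baseline leaves the t-test's standard error correct, only larger. Omitting centre errs slightly on the safe side. In the advanced unit, a chance baseline difference would have a standard error of 8.5 × √(2/28) = 2.3 points if the baseline SD is also 8.5 (assumed), or 31% of the 7.3-point target. That is variance the t-test already counts, not bias.

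**Power is not short.** The trial was sized for the unadjusted test and keeps 88% to 89% after the planned loss. At a correlation of 0.3, with the SD taken as that of final values, the gain is under 3 points. Both remarks are correct, so this is precision forgone and not a failure of the plan.

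**Baseline is partly used.** The percentage-reduction grades depend on it. Grading a continuous score into four classes does not recover what a baseline covariate gives. But if the grades were the primary variable, the ANCOVA power figures would not describe that analysis.

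**The mild unit is different.** Its primary outcome is the time to first addition of levodopa, so the baseline argument and the power figures do not reach its 172 participants.

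**Conclusion.** The point holds as an efficiency improvement for OFF duration and PDQ-39. The named two-group tests are valid but leave out the baseline values and the randomisation strata, and the choice between them is open. Power at 20% loss would rise from 89.0% to 95.7% (moderate) and from 88.4% to 95.3% (advanced) at an assumed correlation of 0.5. Over 0.3 to 0.7, under either reading of the SD, it would be about 91% to 99%. Adjustment gained power in every setting tried. The size of the gain rests on a correlation the documents do not give, on the article's own effects and SDs, and on the continuous score being the variable analysed. Omitting centre inflates the standard error by about 0.5% to 5% at assumed ICCs of 0.01 to 0.10. The documents do not support a claim of invalid tests, of a shortfall against planned power, or of a primary analysis explicitly fixed as unadjusted. The change is advisable, not essential to validity.

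**What to change.** For each of OFF duration (moderate unit) and PDQ-39 (advanced unit), name one primary analysis:

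- an ANCOVA with treatment, baseline value and centre as terms;
- small centres pooled by a rule fixed before unblinding;
- one pre-stated primary time point, for example week 24, the end of treatment;
- a rank-based analysis as the stated sensitivity analysis, in place of the open choice between t-test and Mann–Whitney U.

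State also that the continuous score, not the reduction grade, is the primary variable, if that is the intention. For the mild unit, whatever time-to-event analysis is adopted should be stratified by centre.

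The cost is wording in the protocol or analysis plan. The baseline values are already scheduled, centre is known for every participant, the planned software fits the model, and the sample size need not change.

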Participants can withdraw from the study at any time if they perceive poor efficacy or adverse reactions. Subjects with poor compliance, serious comorbidities or complications, or serious adverse events will be persuaded to quit the study. These subjects will be treated as drop-out cases, and the time and reason for drop-out should be stated. Once the subject drops out, investigators should try to contact the subject as much as possible to inquire about the reason and complete the assessments. The timing of the last medication should also be recorded.

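### The methods named for OFF duration and PDQ-39, if run on observed data, generally need drop-out unrelated to outcome; the protocol expects 20% drop-out, partly for poor efficacy, so bias of unknown size and direction is possible

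*Protocol article*

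**What the plan says.** All references are to the protocol article.

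- **Statistical methods.** Two-group comparisons of measurements use Student's t-test or the Mann-Whitney test. The section continues: "Multivariate analysis will be performed using analysis of variance (ANOVA) or generalized estimation equations (GEE"). No working correlation is given for GEE. The significance rule is "All analyses will use two-tailed tests with a P value of 0.05 as the threshold for significance".
- **Eligibility criteria, withdrawal paragraph.** "Participants can withdraw from the study at any time if they perceive poor efficacy or adverse reactions". Those who leave count as drop-outs. The same paragraph tells investigators to try to reach them, ask why they left and complete the assessments.
- **Sample size.** The totals are set "Considering a 20% drop-out rate". The planning values are "among moderate PD patients was 4.6 min, S.D. 8.3" for OFF duration and "among advanced PD patients was 7.3 points, S.D. 8.5" for PDQ-39.
- **Study setting and Table 2.** In the moderate and advanced units both outcomes are measured at baseline and at weeks 12, 24 and 36, so anyone who leaves after week 12 has an earlier score on file.

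**The concern.** The named methods and the stated reasons for leaving fit together poorly. On observed data, a t-test or Mann-Whitney test at week 24 uses only the patients present at that visit. Repeated-measures ANOVA drops anyone with a missing visit. Unweighted GEE is in general consistent only when data are missing completely at random, and with an independence working correlation its week-24 contrast is the completers' contrast.

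If leaving depends on how a patient is doing, those who remain no longer represent the randomised arms. The week-12 scores that could correct part of this are already collected, but completer tests and independence GEE do not use them. At stake are the primary effect estimates of two of the three units, and their power.

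**Working it through.** **1. Reproduce the plan's numbers.** The inputs are in the Sample size section: "Considering a 5% significance level and a determined 0.10 β value", z values 1.96 and 1.28, and the differences and SDs quoted above. The plan's formula is n per arm = 2[(1.96 + 1.28)·SD/δ]² + 1.96²/4.

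- OFF: 2(3.24 × 8.3/4.6)² + 0.96 = 69.3, rounded up to 70; × 1.2 = 84 per arm, 168 in total.
- PDQ-39: 2(3.24 × 8.5/7.3)² + 0.96 = 29.4, rounded up to 30; × 1.2 = 36 per arm, 72 in total.

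Both totals reproduce. The figures "84 in the moderate PD unit, and 36 in the advanced PD unit" therefore already contain the 20% allowance.

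**2. Loss of numbers alone.** After 20% loss, 84 × 0.8 = 67.2 and 36 × 0.8 = 28.8 per arm remain. Power = Φ(δ/(SD·√(2/n)) − 1.96):

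- OFF: 4.6/(8.3 × √(2/67.2)) − 1.96 = 1.25, power 89.5%.
- PDQ-39: 7.3/(8.5 × √(2/28.8)) − 1.96 = 1.30, power 90.3%.

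Unrelated drop-out is thus already paid for. Any further loss must come from bias.

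**3. Drop-out driven by the observed week-12 score.** The protocol gives no drop-out mechanism, so this is simulation under assumptions: bivariate normal scores at weeks 12 and 24, week 24 taken as the analysis visit, visit correlation 0.5-0.7, about 20% overall loss after week 12, log-odds of leaving rising by 1-2 per SD of worse week-12 score, the same rule in both arms, and no leaver assessed later. There were 4,000 trials per setting. The likelihood estimate of each arm's week-24 mean is the completers' mean + b × (week-12 mean of all − week-12 mean of completers), where b is the slope of week 24 on week 12. For two visits this corresponds to the mixed model.

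| Outcome (true effect) | Effect at week 12 | Completers: estimate | Completers: power | Likelihood model: estimate | Likelihood model: power |
|---|---|---|---|---|---|
| PDQ-39 (7.3) | full | 6.1-6.9 | 79-86% | 7.2-7.3 | 90-92% |
| PDQ-39 (7.3) | half | 6.7-7.1 | 87-90% | 7.3 | 90-92% |
| OFF (4.6 min) | full | 3.8-4.4 | 80-87% | 4.6 | 90-92% |
| OFF (4.6 min) | half | 4.2-4.5 | 87-90% | 4.6 | 90-92% |

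The extremes are 3.8/4.6 = 83% and 4.5/4.6 = 98% of the true effect, a shrinkage of about 2-17%.

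**4. GEE.** OFF duration, true effect 4.6, large simulated data sets, drop-out on the week-12 score:

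- Half effect at week 12: independence 4.31-4.33, exchangeable 4.51-4.58.
- Full effect at week 12: independence 3.79-4.25, exchangeable 4.48-4.57.

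The half-effect runs had 15,000 per arm, so with 20% loss the simulation error is about 8.3 × √(2/12,000) = 0.11. With two visits there is only one correlation, so exchangeable and unstructured coincide.

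**5. Leavers still assessed.** If half of the leavers are assessed (an assumed fraction) and the full effect is present at week 12, completer estimates are 6.9-7.1 and 4.35-4.50. Power is 89-92%.

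**6. Other mechanisms.**

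- Drop-out driven by the unseen week-24 value (slope 0.5-2, correlation 0.6, half effect at week 12): completers keep 76-97% of the effect, power 79-88%. At slope 2 the completer estimates are 3.50 and 5.62; the likelihood estimates are 3.78 and 6.05, better but still biased.
- Poor responders leaving mainly from active treatment (about 30% v 10%): the completers' effect rises to 6.76 min (147%) and 9.51 points (130%), with power about 99%.

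**The case against.** **Left to the analysis plan.** The article's statistical paragraph is a condensed list. The sentence on ANOVA and GEE is not tied to these two outcomes, and imputation before the t-test or weighting of the GEE would be compatible with it. A reader might infer that the protocol is at fault for stating no analysis set or missing-data method. That is not supported, because such details may stand in an analysis plan that is not shown. What remains is a point about methods the article does name, in its only analysis text for these outcomes.

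**Direction.** A reader might infer that the effect will shrink and power will fall. The documents do not support this as a plain statement. Adverse reactions stand beside poor efficacy as a reason to leave, and step 6 shows inflation when poor responders leave mainly from active treatment. With no treatment effect and the same rule in both arms, the t-test stays unbiased.

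**All named methods fail alike.** A reader might also infer that none of them uses the earlier scores. That is wrong for GEE with an exchangeable working correlation, which recovers nearly all of the effect in step 4. The article leaves the working correlation open.

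**Retrieval.** Drop-out is not the same as a missing outcome, since investigators are told to try to complete the assessments. If they succeed for half of the leavers, most of the loss disappears. The success rate is unknown, so this lessens the concern without removing it.

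**The remedy has limits too.** The mixed model is also biased when drop-out depends on unseen values. That stands.

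**Conclusion.** The point holds in conditional form. On observed data, the t-test, Mann-Whitney test, ANOVA and unweighted GEE are in general unbiased for OFF duration and PDQ-39 only when drop-out is unrelated to outcome, and the protocol itself names an outcome-related reason for leaving. The bias is of unknown size and direction. Under a common rule for poor responders, the assumptions of step 3 give the 2-17% shrinkage and power of 79-90%. The lower end needs the full effect by week 12, a steep slope and no retrieval together; with half the effect at week 12, power is 87-90%, close to the 89-90% expected from loss of numbers alone. In the step 3 settings the likelihood model was essentially unbiased and at least as powerful as the completer test. This is a worthwhile improvement to a stated choice, of moderate weight, and does not show that the planned analyses will fail.

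**What to change.** For OFF duration and PDQ-39, name as primary analysis a likelihood-based mixed model for repeated measures on all post-baseline visits, with arm, visit and arm-by-visit terms and an unstructured covariance. Include assessments obtained after drop-out, and take the primary contrast at the chosen visit. Keep the t-test and GEE as sensitivity analyses, and state the working correlation for GEE.

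The cost is wording in the protocol or analysis plan; the visits are already scheduled and no new data are needed. The small downside is a model-based result in place of a simple test. That result is valid when drop-out depends on observed scores, but not when it depends on unseen values.
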